### Randomization and Masking

The study group consisting of socket preservation with ADG and T-PRF or the control group consisting of DFDBA and T-PRF will be randomly assigned. Every patient will be required to complete a comprehensive medical history form, give informed consent, and receive a thorough description of the study. A secure computer system will be used for central randomization in this procedure. A distinct study code will be given to each patient, and the operators and research evaluators will receive their data in a format that maintains patient confidentiality through coding. The radiologist and the statistician will be blinded to the treatment while analyzing the data. Blind quantitative histological analysis will be performed by a trained specialist.

### Clinical Procedure

#### Presurgical Phase

Patients will be clinically examined for periodontal diseases. Every patient will be required to complete a comprehensive medical history form, give informed consent, and receive a thorough description of the study. Following a comprehensive clinical examination and radiographical diagnosis, initial therapy will consist of guidance on maintaining good oral hygiene and a full mouth ultrasonic scaling procedure. Patients will receive plaque control instructions until their plaque score is less than 25%. Before any surgical procedure, a diagnostic cast will be made for every patient to ascertain the maxilla-mandibular relationship. Clinical photographs will be captured throughout the procedure. CBCT images will be obtained for every participant.

#### Preparation of T-PRF

Just prior to the surgery, by venipuncturing the antecubital vein, 10 mL of venous blood will be obtained under aseptic conditions and transferred to a new, sterile titanium tube. T-PRF is an autogenous blood concentrate of the third generation, characterized by a thick and durable fibrin meshwork that is triggered by a titanium tube [12]. Centrifugation is performed for 15 minutes at 3500 rpm. After transferring the resulting T-PRF clot onto a PRF box and separating it with sterile tweezers and scissors, the serum will be squeezed out of the clot to create a stable fibrin membrane [13]. A portion of the membrane is chopped up for use as graft material, and the remaining portion will be trimmed to fill the defect with membrane.

#### Surgical Procedure for the Test Group

Patients are instructed to gargle for 1 minute with 0.12% chlorhexidine gluconate. Local anesthesia will be administered. In order to minimize the surgical trauma during the flapless tooth extraction process, periotomes and forceps will be used. Using a number 15 blade, a crevicular incision will be created, removing periodontal ligament fibers on the distal and mesial sides. The teeth will be carefully luxated using elevators. Precautions will be taken to prevent trauma to the adjacent tissues. After tooth extraction, bone curettes will be used to completely debride the socket's granulation tissue. Initially, a high-speed handpiece will be used to remove any debris, artificial material, rot, and gutta-percha from the extracted roots, leaving just the clean tooth root. The roots that contain dentin will be crushed using a dentin grinder (Figure 2).

**Figure 2 figure2:**
[figure not shown]
Dentin grinder.

The generated root dentin particle material will be treated through 3 steps. First, the dentin cleansing solution is poured into the dish containing the particles and allowed to sit at room temperature for 5 minutes. The solution is then allowed to dehydrate using a sterile gauze. Second, the particle is then totally covered with phosphate-buffered saline, which is then put into the plate (Figure 3).

**Figure 3 figure3:**
[figure not shown]
Dentin cleanser and buffered saline solutions.

The particle is mixed with fresh sterile gauze to dehydrate it by using a sterile device. With the phosphate-buffered saline solution, this step is repeated once more. To neutralize the pH levels, this step is crucial. At last, the ADG, whose particle size ranges from 300 to 1200 microns is prepared for prompt grafting (Figure 4).

**Figure 4 figure4:**
[figure not shown]
Extracted tooth sample.

The extraction sockets will be filled with a mixture of T-PRF and ADG (Figure 5). After enclosing the resistant bone with a collagen plug, nonresorbable suturing material is used to sew the plug to the surrounding soft tissues.

**Figure 5 figure5:**
[figure not shown]
Prepared autologous dentin graft.

#### Surgical Procedure for the Control Group

DFDBA, a completely resorbable alloplastic bone substitute, will be inserted into the extraction socket together with T-PRF following an atraumatic extraction. It is important to exercise caution when filling the socket after applying the graft since this could cause the exposed coronal particles to get sequestered or cause the graft mass to disperse as a whole. T-PRF is applied to compact the graft particles even more and accelerate in-situ healing.

#### Postsurgical Care

Participants will be given explicit instructions not to eat or drink anything hot on the surgical site nor should they rinse their mouths vigorously. All the patients will receive antibiotics (amoxicillin capsule 500 mg every 8 hours, metronidazole tablets 400 mg every 8 hours) and analgesics (Ibugesic tablets every 8 hours) after surgery for a period of at least 3 days. Two weeks following the surgical procedure, participants are recommended to gently brush the area surrounding the surgical site; nevertheless, regular tooth brushing should be continued for the remaining areas of the dentition starting on the day following the procedure. In addition, 2 weeks of twice-daily mouthwash containing 0.2% chlorhexidine is prescribed. Seven days following the procedure, the sutures will be removed.

#### Follow-Up

A complete examination will be conducted at the 4-month follow-up appointment [14]. Every clinical variable will be evaluated. A clinical and radiographic evaluation will be performed. Histomorphometric analysis will be performed on the bone obtained by trephine bur during implant placement.

### Statistical Analysis

Mean (SD) values will be found for each clinical periodontal parameter such as plaque index, papillary bleeding index, probing pocket depth, width of keratinized gingiva, clinical attachment level, and marginal bone level. Next, from baseline to 4 months, the mean data will be statistically analyzed. To equate baseline to 4-month findings for every patient, Student paired *t* test will be employed for intragroup data comparison, while the Student unpaired 2-sided *t* test will be utilized for intergroup comparison. If the *P* value exceeds .05, the observed difference will be considered nonsignificant; if it remains below .05, it will be considered significant.

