**Objective:**

The aim of this study is to evaluate and compare the effectiveness of alveolar socket preservation by using demineralized freeze-dried bone allograft (DFDBA) with titanium platelet-rich fibrin (T-PRF) and autologous dentin graft (ADG) with T-PRF. This assessment will be performed through comprehensive clinical, radiographic, and histomorphometric analyses. The primary objective of this study is to histologically evaluate the new bone formation in the extraction sockets preserved using either DFDBA with T-PRF or ADG with T-PRF. The secondary objective is to evaluate the dimensional changes, including ridge width and height at these healing points, as measured by clinical and radiographic methods. We will evaluate and compare the clinical, radiographic, and histomorphometric outcomes of using DFDBA with T-PRF versus ADG with T-PRF for maintaining socket integrity after tooth extraction. We will also ascertain which grafting technique facilitates the production of new bone during the healing phase and preserves alveolar ridge dimensions.

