**Methods:**

This randomized controlled trial will involve 16 patients aged 22-60 years requiring tooth extractions and subsequent implant placement. Participants will be randomly assigned to one of the 2 groups: (1) socket preservation using DFDBA in combination with T-PRF or (2) socket preservation using ADG with T-PRF. At baseline, all the clinical variables will be assessed using UNC-15 probe and cone beam computed tomography radiographs. Extraction will be done atraumatically with minimal flap reflection by using periotomes. Postextraction sockets will be preserved using DFDBA+T-PRF or ADG+T-PRF. At 4 months, clinical and radiographic evaluations will be done, and the implant will be placed using a 2-stage protocol. Histomorphometric analysis will be performed after receiving bone samples during implant placement. At 3 months after implant placement, the second-stage surgery will be done.

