### Primary Outcomes

Four months following the socket preservation procedure, the formation of new bone and changes in the alveolar socket dimensions in both groups will be assessed by radiological and histomorphometric analyses. Histomorphometric evaluations will be performed on bone core biopsies obtained at the time of implant placement at 4 months after the extraction. These samples will be processed using standard histological techniques, stained with hematoxylin and eosin, and assessed under light microscopy. Quantitative measurements such as the percentage of new bone formation, number of osteocytes, and trabecular patterns will be analyzed using Planmeca Romexis software (version 6.2.0; Planmeca Oy) to determine the measurement of bone dimensions, apico-coronal ridge height, and density in Hounsfield units.

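### The between-arm t test has no stated scale and no baseline covariate; with 8 patients per arm, a baseline-adjusted comparison of ridge and soft-tissue dimensions would usually be more precise

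*Protocol article*

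**What the plan says.** The Statistical Analysis section of the protocol article fixes two tests and one significance rule (P below .05). The sentence that assigns the tests reads in part "test will be employed for intragroup data comparison, while the Student unpaired 2-sided", and the unpaired "test will be utilized for intergroup comparison". No covariate is named. The scale of the unpaired test is left open: the text says only that "from baseline to 4 months, the mean data will be statistically analyzed".

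The section gives examples of clinical periodontal parameters, including "probing pocket depth, width of keratinized gingiva, clinical attachment level, and marginal bone level". The list is introduced as examples, so it is open. Ridge width, ridge height and soft-tissue thickness are not named, but no other analysis text covers outcomes measured at baseline and at 4 months.

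The baselines exist. The Abstract (Methods) states: "At baseline, all the clinical variables will be assessed using UNC-15 probe and cone beam computed tomography radiographs". The Presurgical Phase section has CBCT images taken for every participant, and the Follow-Up section repeats the clinical and radiographic evaluation at 4 months.

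The dimensional outcomes are worded as changes. The Abstract (Objective) says "The secondary objective is to evaluate the dimensional changes, including ridge width and height at these healing points". Under Primary Outcomes, "the formation of new bone and changes in the alveolar socket dimensions in both groups will be assessed by radiological and histomorphometric analyses". The Secondary Outcomes section likewise describes linear changes in soft tissue and in midfacial and midpalatal bone, measured at baseline and at 4 months.

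**The concern.** Three features of the plan matter together.

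- **The paired tests do not compare the grafts.** The Introduction describes ridge resorption after extraction as physiological, so change is expected in both arms. A significant change in one arm and not in the other is no evidence that the arms differ.
- **The scale of the unpaired test is not fixed.** A test on 4-month values and a test on changes have different power and can give different answers on the same data.
- **Neither version adjusts for baseline.** Single teeth are enrolled without restriction on position in the Inclusion Criteria, so baseline ridge size will probably vary between patients. With 8 per arm, sizeable chance imbalance is likely.

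At stake is precision where it is scarcest, and an estimate of the dimensional difference that chance baseline imbalance can shift either way.

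**Working it through.** **The plan's own figure.** The Sample Size Calculation gives means 0.72 and 1.33, SDs 0.23 and 0.24, α = .01, β = .01 and ratio 1. The difference is 0.61 and the pooled SD is √((0.23² + 0.24²)/2) = 0.2351. The two-sided normal formula gives n = 2 × (0.2351 × (2.576 + 2.326)/0.61)² = 7.14, rounded up to 8 per group. This agrees with the protocol. These inputs are for newly formed bone, so the present point does not change the sample size.

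**Inputs for the comparison.** n = 8 per arm, N = 16, two-sided 5% level (Statistical Analysis). The correlation ρ between baseline and 4-month values is not in the document and is assumed over a range. Equal SDs at baseline and 4 months are also assumed.

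**Variance of the arm difference, relative to a t test on 4-month values:**
- change score: 2(1 − ρ)
- ANCOVA: (1 − ρ²) × (N − 3)/(N − 4) = (1 − ρ²) × 13/12, where 13/12 is the average cost of covariate imbalance

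**Ratio of 95% CI widths.** ANCOVA has 13 residual degrees of freedom against 14, so the t quantiles contribute 2.160/2.145 = 1.007.
- Against 4-month values: √((1 − ρ²) × 13/12) × 1.007
- Against change scores: √(((1 + ρ)/2) × 13/12) × 1.007, because (1 − ρ²)/(2(1 − ρ)) = (1 + ρ)/2

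| ρ | ANCOVA vs 4-month values | ANCOVA vs change scores |
|---|---|---|
| 0 | 1.048 | – |
| 0.3 | 1.000 | – |
| 0.5 | 0.908 | 0.908 |
| 0.7 | 0.749 | 0.967 |
| 0.8 | 0.629 | 0.995 |
| 0.9 | – | 1.022 |

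Setting each ratio to 1 gives break-even at ρ of about 0.30 against 4-month values and about 0.82 against change scores.

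**What this means for power.** The detectable difference at 80% power is in SD units. Power is simulated at a true difference of 1 SD, with 40,000 trials per setting. Each cell gives 4-month t test / change-score t test / ANCOVA.

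| ρ | Detectable difference | Power |
|---|---|---|
| 0.5 | 1.51 / 1.51 / 1.37 | 46% / 46% / 54% |
| 0.7 | 1.51 / 1.17 / 1.13 | 46% / 67% / 70% |
| 0.8 | 1.51 / 0.95 / 0.95 | 47% / 84% / 84% |
| 0.9 | 1.51 / 0.67 / 0.69 | 46% / 99% / 98% |

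With no true difference, all three tests rejected in about 5% of trials.

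**Chance imbalance.** The standard error of the baseline mean difference is √(2/8) = 0.5 SD, so an imbalance beyond 0.5 SD in either direction arises in about 32% of trials. An imbalance of d shifts the expected 4-month difference by ρd and the expected change difference by (ρ − 1)d. At ρ = 0.7 and d = 0.5 SD these are 0.35 SD and −0.15 SD.

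**Paired tests.** If both arms have the same true change and each paired test has power p, exactly one arm is significant with probability 2p(1 − p). That is 50% at p = 0.5 and 32% at p = 0.8. Simulation with standardised within-arm changes of 0.5, 0.75 and 1.0 gave 35%, 50% and 43%.

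**The case against.** A reader might infer that the plan ignores the baseline. The document does not support that. The scale of the unpaired test is unstated, and the objective and both outcome sections word these outcomes as changes, so a t test on changes is arguably the more natural reading. Such a test uses the baseline, and the gain from ANCOVA is then modest: 3% at ρ = 0.7, under 1% at 0.8, and a loss of about 2% at 0.9. Mixed tooth positions may push ρ upward, which is where change scores do well. This objection stands, and it limits the size of the point.

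A reader might also infer that the arms are not properly compared, or that paired P values will be used to claim superiority. Neither follows. The unpaired test is assigned to the between-arm comparison and is valid under randomisation, and its 5% error rate already allows for chance imbalance. The plan gives the paired tests no comparative role. The 32% to 50% discordance shows why they should not acquire one; it does not describe a stated misuse.

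Applying the section to ridge dimensions is an inference, since they are not named. It is a reasonable one, because the list is open and no other text covers these outcomes.

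Finally, covariate adjustment is often left to an analysis plan, and this is a condensed article. Here, however, the article names the tests. The point concerns a stated method, not an absent detail.

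**Conclusion.** The point holds as a recommended improvement for the dimensional outcomes, not as an error that invalidates the analysis. The between-arm test is named without its scale and without the baseline that every patient supplies.

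The size of the gain depends on which test is meant and on a correlation that the document does not give. It is substantial against 4-month values at moderate or high correlation, and small to nil against change scores once the correlation reaches about 0.8. ANCOVA is therefore not more precise in every case. Its losses at the extremes are small, about 5% of CI width at ρ = 0 against 4-month values and about 2% at ρ = 0.9 against change scores, and choosing it does not require ρ to be known in advance. The figures against change scores also rest on equal SDs at the two visits.

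The conclusion does not extend to histological new bone, the subject of the primary objective, which is measured once and has no baseline to adjust for.

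**What to change.** In the Statistical Analysis section, name ridge width, ridge height and soft-tissue thickness. For each, state that the inferential between-arm analysis is an ANCOVA of the 4-month value on arm with that measure's own baseline as covariate, reported as the adjusted difference with its 95% CI. This also settles the scale. State that within-arm baseline to 4-month changes are descriptive and that paired P values will not be used to compare the grafts.

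The cost is a sentence or two of text, one residual degree of freedom (13 instead of 14), a linearity assumption, and a slight loss of precision if the correlation is very low or very high. No extra patients or measurements are needed.

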## Results

This study received ethical approval in January 2024. Enrollment began from March 2024. The study commenced in August 2024 and is scheduled to conclude postassessments and analyses by the end of 2025. The results of the study are anticipated to be accessible in late 2025. Results will be shared using a variety of methods, including research reports, scholarly publications, and attendance at international conferences. A primary manuscript intended for submission to a prestigious, high-impact, peer-reviewed journal will elaborate on the findings related to the primary objective.

## Discussion

Socket preservation is a fundamental technique in dentistry, preserving alveolar bone structure after the extraction to facilitate optimal healing and support future dental restoration procedures. This study primarily focuses on histomorphometric analysis, which is considered a highly sensitive and accurate method for assessing new bone formation. Due to the precise and quantitative nature of histological outcomes, a smaller sample size can yield reliable and clinically meaningful data compared to studies relying solely on radiographic or clinical endpoints.

Hussain et al [4] demonstrated promising outcomes regarding the utilization of ADG in alveolar ridge preservation. Their study revealed superior dimensional stability in the study group compared to the control group, as evidenced by standardized CBCT scans. The study group's successful graft remodeling was further validated by histomorphometric analysis, demonstrating the potential of using ADG for effectively retaining the dimensional integrity of ridges. These findings highlight the need to utilize innovative biomaterials such as ADG to enhance clinical results and facilitate optimal wound healing.

Bhombe et al [5] investigated the use of PRF matrix and DFDBA as adjuvants during immediate implant placement procedures following tooth extraction. Their findings indicate that using PRFM and DFDBA in jumping gap distance as adjuvants resulted in significant coronal bone remodeling and a significant decrease in bone resorption.

In another clinical study by Elfana et al [15], histomorphometric findings demonstrated that the autogenous whole tooth and autogenous demineralized dentin graft groups exhibited higher proportions of newly formed bone (48.40%). The histology study confirmed that both types of transplants were compatible with the host tissues and showed no symptoms of inflammation.

Dwivedi et al [16] demonstrated that chair-side autogenous tooth grafts offer several advantages, including greater primary implant stability, faster recovery times, ease of preparation, reduced rates of bone resorption, and qualities that promote bone growth and socket augmentation.

ADG, which has both osteoconductive and osteoinductive qualities, appears to be a promising alternative for alveolar ridge preservation treatments, according to a systematic study by Sánchez-Labrador et al [17]. Positive outcomes in terms of volume preservation and histomorphometric data were noted; they were reinforced by the properties of materials, such as low complication rate and cost-effectiveness in comparison to alternative bone substitutes.

Thus, the purpose of this study is to assess and compare the effectiveness of DFDBA with T-PRF and ADG with T-PRF in socket preservation by performing clinical, radiological, and histomorphometric analyses. This study plan will be reliable to prove advantages pertaining to improvements in the maintenance of vertical and horizontal socket dimensions and phenotypic dimensions.

## Appendix

Multimedia Appendix 1 CONSORT 2010 checklist.

## Abbreviations

ADG: autologous dentin graft
BMP: bone morphogenetic protein
CBCT: cone beam computed tomography
CONSORT: Consolidated Standards of Reporting Trials
DFDBA: demineralized freeze-dried bone allograft
PRF: platelet-rich fibrin
T-PRF: titanium platelet-rich fibrin
